Specific monitoring will be performed for retinal toxicity, which is a recognized side effect of ethambutol and has been observed in some animal species after prolonged dosing of moxifloxacin (though not reported in clinical trials or post-marketing surveillance of moxifloxacin). Monitoring for retinal toxicity will consist of visual acuity and color vision testing per standard site practice. Laboratory monitoring will consist of a CBC, serum AST, bilirubin, and creatinine, and will be obtained at 2, 4, 6, 8, and 12 weeks. Because significant cardiotoxicity has not been observed among the over 10 million patients treated with moxifloxacin after its approval and is not associated with the duration of treatment in animal models, electrocardiographic monitoring will not be done during this study.

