### Drug-drug interactions

Interaction studies have been performed with moxifloxacin and theophylline[68], warfarin, digoxin, probenecid[69], ranitidine, glyburide[70], iron[71], calcium supplements[72], sucralfate[73], and antacids[74]. Only a few clinically significant interactions have been described. All fluoroquinolones can bind to multivalent cations (esp. Fe+3, Al+3, and Mg+2, but not Ca+2], with resultant substantial (40-60%) decreases in absorption when taken concurrently. Moxifloxacin should not be administered at the same time as antacids containing magnesium and/or aluminum, sucralfate, antidiarrheals that contain kaolin, or iron and/or zinc containing medications or supplements.

Rifampin induces the activity of the phase II enzymes glucuronosyltransferase and sulphotransferase [75]. Interaction studies between rifampin and moxifloxacin have not been performed. However, because glucuronidation is a minor pathway in moxifloxacin metabolism (accounting for approximately 20% of total hepatic metabolism), a significant interaction between rifampin and moxifloxacin is unlikely.

Tolerability

As a class, fluoroquinolones are considered to be safe and relatively free of serious adverse effects[76]. The safety and efficacy of moxifloxacin for the treatment of community acquired bacterial infections has been extensively studied, and the drug is approved in the U.S. as a 10-day course of treatment for upper and lower respiratory tract infections.

In the usual daily doses of 400 mg/day, moxifloxacin is well tolerated. Expected minor adverse events have occurred with a frequency similar to that for other fluoroquinolones in similar populations. Gastrointestinal adverse effects are the most common, and they include nausea (7%), diarrhea (6%), dizziness (3%), abdominal pain (2%), vomiting (2%), dyspepsia (1%), and taste perversion (1%). There are no current reports of hepatitis, although abnormal liver function tests have been noted in 1% of patients.

Of note, fluoroquinolones are generally used short-term for acute conditions. However, fluoroquinolones have been found to be safe and effective in long term use for chronic infections such as osteomyelitis, prostatitis, or chronic urinary tract infection, or skin and skin structure infections[76, 77]. In addition, Valerio et al. found that the combination of moxifloxacin, isoniazid, and rifampin given for 6 months was well tolerated[32].

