### Toxicity

Ethambutol is usually well-tolerated with low rates of skin rash, nausea, vomiting, or diarrhea. Fever, allergic reactions, abdominal pain, mental status changes, peripheral neuropathy, and increased liver function tests have rarely been associated with ethambutol. Adverse events occur in less than 2% of patients receiving ethambutol at the 15 mg/kg dose and include decreased visual acuity (0.8%), rash (0.5%) and asymptomatic hyperuricemia[86]. The most common serious side effect of ethambutol is retinal toxicity, often first perceived as a decrease in color perception. Patients receiving ethambutol should be instructed about symptoms of ocular toxicity. If stopped promptly, permanent visual loss is rare among patients with ethambutol-related retinal toxicity. Rates of retinal toxicity are very low when the drug is given for relatively short periods of time, as is the case in this study.

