### Toxicity

The total incidence of all adverse effects from isoniazid is approximately 5%, many of which do not require discontinuation of the drug. Peripheral neurotoxicity is dose dependent and it is uncommon (<0.2%) at conventional doses. The risk of peripheral neuritis increases for persons who are malnourished or predisposed to neuritis by other illnesses. Concomitant administration of pyridoxine (vitamin B6) is recommended for these persons, and will be given to all patients in this trial. Other nervous system reactions are rare at normal doses, and they include convulsions, encephalopathy, optic neuritis, memory impairment, and psychosis. Gastrointestinal adverse effects include nausea, vomiting, and epigastric distress.

Asymptomatic elevation of aminotransferases is common and occurs in 10-20% of persons receiving isoniazid. However, idiosyncratic severe hepatic reactions are uncommon but are more likely in older persons (up to 2.3% hepatitis incidence in persons more than 50 years old), and may be life threatening. Daily consumption of alcohol increases the risk of isoniazid-associated hepatotoxicity by approximately four-fold. The risk of isoniazid-induced hepatotoxicity may also be increased in the postpartum period. The prodromal symptoms of hepatotoxicity are anorexia, nausea, vomiting, fatigue, malaise, and weakness; persons who take isoniazid and have these symptoms should stop therapy and be evaluated immediately.

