In general, for grade 1 toxicities, the patient will be followed carefully and the study drugs will be continued. For grade 2 toxicities, the patient will be followed more carefully, with additional laboratory and/or clinic visits as necessary, and the study drugs temporarily held at the investigator's discretion. For any grade 3 toxicity that, in the principal investigator’s judgment is due to study drug(s), the causative study drug(s) should be held. The clinician should rule out other possible causes of the symptoms before discontinuing study medication. When possible, concomitant medications should be held first at the discretion of the principal investigator if he/she suspects they are contributing to the toxicity. Depending on the nature and severity of the toxicity, the degree to which it resolves, and/or the emergence of alternative explanations for the toxicity or the subject’s deterioration, the study drugs(s) may be restarted at the discretion of the investigator. For any recurring grade 3 or grade 4 toxicity, the study drugs should be temporarily held and may be permanently stopped at the discretion of the investigator.

Any patient with grade 4 renal, hepatic, cardiac or hematological toxicity will be immediately discontinued from study therapy. The laboratory test or clinical finding in question will be reassessed as soon as possible. The repeat test will guide management of the event as follows:

- If the repeat assessment shows toxicity of grade 3 or lower, and if the patient has continued to receive study drugs between the two testing dates, then the patient will be managed according to the appropriate toxicity level of the repeat test.
- If the repeat test shows toxicity of grade 3 or lower, and if the patient has not received study drugs between the two testing dates, then the patient will be managed at the discretion of the investigator with regard to the re-administration of study drugs, and otherwise according to the toxicity level of the repeat test.
- If the repeat test shows grade 4 toxicity, then the patient will be permanently discontinued from study medications. Further treatment of TB will be directed by the investigator on an individualized basis. The patient will continue to be followed for study monitoring purposes (as are other patients who make a permanent departure).

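### Sections 2.2 and 5.5 of the protocol give different instructions for mild hepatitis-type symptoms, and because isoniazid is blinded the conflict reaches both arms

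*Protocol*

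**What the plan says.** Section 5.5 sets out a ladder by grade. At the bottom: "In general, for grade 1 toxicities, the patient will be followed carefully and the study drugs will be continued". At grade 2 the patient is watched more closely, with "the study drugs temporarily held at the investigator's discretion". At grade 3 a drug judged responsible should be held. The same paragraph adds: "The clinician should rule out other possible causes of the symptoms before discontinuing study medication". The section makes no exception for symptoms that may signal hepatitis.

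Section 2.2, in the isoniazid toxicity text, says: "The prodromal symptoms of hepatotoxicity are anorexia, nausea, vomiting, fatigue, malaise, and weakness". It continues that "persons who take isoniazid and have these symptoms should stop therapy and be evaluated immediately". No grade is attached.

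Section 5.3 has all symptoms graded by the modified Common Toxicity Criteria in Appendix E. Section 5.9 states that rifampin, pyrazinamide and ethambutol are open-label. Isoniazid and moxifloxacin are given against matching placebos. Section 3.5 makes discontinuation of the assigned regimen for any reason the primary safety and tolerability endpoint.

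**The concern.** A site that meets a patient with new loss of appetite or mild nausea has two places in the protocol to look, and they point in different directions. The first question is patient safety: hepatotoxicity is a known risk of isoniazid and pyrazinamide. The protocol's own discussion of rifampin/pyrazinamide toxicity also raises the possibility that isoniazid lessens it, and the experimental arm leaves isoniazid out. Sites should therefore handle suspected hepatitis in one way.

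The second question is the data. Discontinuation for any reason is a primary endpoint, and in section 5.3 the work-up for viral hepatitis is triggered by hepatic toxicity that requires stopping study drug. If sites differ in when they stop, they may also differ in who is worked up and, where a stop becomes permanent, in who counts as discontinued.

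**Working it through.** The protocol gives no figure on this point, so the check is a comparison of text.

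**Step 1: grade the symptoms named in section 2.2 by Appendix E.**

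| Symptom | Appendix E, grade 1 (paraphrased) | Section 5.5 at grade 1 | Section 2.2, isoniazid |
|---|---|---|---|
| Anorexia | appetite lost, with no stated fall in intake | continue | stop and evaluate |
| Nausea | patient can still eat | continue | stop and evaluate |
| Vomiting | a single episode in a day above pretreatment | continue | stop and evaluate |
| Fatigue or malaise (one row) | more tired than at baseline, normal activities unaffected | continue | stop and evaluate |

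Weakness is less clear. Asthenia sits in the fatigue row, but the separate muscle-weakness row keeps grade 1 for an asymptomatic finding on examination. The point does not depend on it.

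**Step 2: compare the actions by grade.**

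- Grade 1: section 5.5 continues and section 2.2 stops. These conflict.
- Grade 2: section 5.5 permits a hold and section 2.2 calls for one. These are inconsistent, but a site that stops at grade 2 complies with both.
- Grade 3: section 5.5 says to hold a drug judged responsible, so the gap is smaller.

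**Step 3: compare the order of events.** Section 2.2 stops and evaluates at once. Section 5.5 wants other causes excluded before study medication is discontinued. That sentence follows the grade 3 rule, but its wording is not limited to grade 3.

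**Step 4: ask to whom the section 2.2 sentence applies.** It is addressed to people taking isoniazid. Under the blind, a site does not know who they are. It can apply the sentence to every patient, including those on moxifloxacin with isoniazid placebo, or to none. Unblinding does not resolve this in practice. Section 5.9 allows a request for a patient who has already met the criteria for stopping study drug, gives the reviewing team up to two working days, and keeps the code-break card for emergencies. A patient with grade 1 symptoms handled under section 5.5 has not met those criteria.

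**Step 5: ask what can be quantified.** The documents give no rate of grade 1 prodromal symptoms by arm under the trial regimens, no share of such holds that would become permanent, and no statement on whether a temporary hold counts toward the endpoint. The effect on the discontinuation proportion cannot be sized.

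**The case against.** The best defense is that section 2.2 is drug background. The isoniazid text describes toxicity in general, and where it states a trial procedure (vitamin B6 for all patients) it says so. Sections 5.7 and 5.8 refer to the toxicity management text for decisions to stop, while section 5.4 cites section 2.2 only for common adverse effects. Section 5.5 also opens with a general qualifier, and section 5.8 lets the investigator stop on judgment, so a site that stops for suspected hepatitis breaches nothing.

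Much of this stands and softens the conflict. It does not remove it. The section 2.2 sentence is worded as an instruction, in a section to which section 5.4 sends sites. The qualifier and the discretion clause allow departure from the ladder without saying when. Two sites that each follow the text can still treat the same patient differently.

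Three stronger readings are tempting, and the documents do not support them.

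- *That the same contradiction exists for visual toxicity.* The ethambutol text states a prognosis, "If stopped promptly, permanent visual loss is rare among patients with ethambutol-related retinal toxicity", and its only directive is to inform patients about symptoms. Ethambutol is open-label, so the blinding argument does not apply. Blurred vision in Appendix E has no grade 1 entry and begins at grade 2, where section 5.5 allows a hold.
- *That mild findings on the scheduled vision tests would be lost unless reported as adverse events.* The protocol does not make the Adverse Event Form the only route by which scheduled test results reach the analysis, and the case report forms are not shown. An added reporting rule would be a preference.
- *That discontinuation in the moxifloxacin arm could swing by 7 percentage points.* The arithmetic is 205 × 0.07 = 14.4 patients, using the 7% nausea rate in section 2.2. It treats every hold as a discontinuation, although section 5.6 has temporarily stopped patients restarted as soon as possible. It assumes the grades, and it has no control-arm figure although nausea and vomiting are listed for isoniazid and rifampin too. The 7% describes general moxifloxacin use. Table 6, from a randomized levofloxacin trial in tuberculosis, shows nausea or vomiting in 0% and 1.2% over two months.

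**Conclusion.** The point holds for mild prodromal hepatitis symptoms only. At grade 1 the two sections give opposite instructions. At grade 2 they are inconsistent without being irreconcilable. Blinding of isoniazid extends the problem to both arms.

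The main consequence is a patient-safety inconsistency. Some site-dependent variation in discontinuation of assigned therapy may follow, but neither its size nor any difference between arms can be derived from the documents. The conclusion assumes that a site could reasonably read the section 2.2 sentence as operative. If every site treats section 2.2 as background only, the conflict has no practical effect, but the protocol does not tell them to. No view is taken here on which instruction is clinically right.

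**What to change.** Reconcile the two passages. Section 5.5 should state whether the grade ladder or the isoniazid instruction in section 2.2 governs prodromal hepatitis symptoms while isoniazid is blinded. It should also say whether that applies to all patients on blinded medication, and whether the sentence on excluding other causes first covers these symptoms. Section 2.2 should then be made to agree or should refer to section 5.5. The investigators must choose the rule.

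The cost is a few sentences in a protocol amendment and a note to sites. No visit, test, form or sample-size change is needed.

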### Exclusion criteria

1. Breast-feeding
2. Known intolerance to any of the study drugs
3. Known allergy to any fluoroquinolone antibiotic
4. Concomitant disorders or conditions for which moxifloxacin, isoniazid, rifampin, pyrazinamide, or ethambutol are contraindicated. These include severe hepatic damage, acute liver disease of any cause, and acute uncontrolled gout.
5. Current or planned therapy during the intensive phase of tuberculosis treatment using drugs having unacceptable interactions with rifampin (rifabutin can be substituted for rifampin during the continuation phase of therapy)
6. Current or planned antiretroviral therapy during the intensive phase of tuberculosis treatment
7. History of prolonged QT syndrome or current or planned therapy with quinidine, procainamide, amiodarone, sotalol, disopyramide, ziprasidone, or terfenadine during the intensive phase of tuberculosis treatment.
8. Pulmonary silicosis
9. Central nervous system TB

Primary endpoints

1. The proportion of patients having a negative sputum culture at 2 months of therapy
2. The proportion of patients who discontinue assigned study therapy for any reason during the first 2 months

Study Management

Patients will have study visits every two weeks during the first 2 months of therapy. At each study visit, there will be a clinical assessment for toxicity and a sputum specimen will be obtained for smear and culture (two sputum specimens will be obtained after 8-weeks). Mycobacterial cultures must include an approved broth culture system, supplemented by at least one solid medium. Patients who are unable to produce an expectorated sputum specimen at weeks 2, 4, 6, or 8 will have sputum induction.

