### To compare the safety and tolerability of the moxifloxacin regimen to that of the isoniazid regimen

### To determine the time to culture-conversion of the moxifloxacin regimen and the isoniazid regimen using data from 2-, 4-, 6-, and 8-week cultures

- To compare the proportion of patients with any Grade 3 or 4 adverse reactions
- To compare adverse events and 2-month culture conversion rates among HIV-infected patients vs. HIV-uninfected patients
- To compare the rates of treatment failure of the moxifloxacin regimen and the isoniazid regimen
- To determine whether there is delayed toxicity attributable to moxifloxacin (toxicity that becomes evident after the 8 weeks of moxifloxacin therapy)
  1. Study Endpoints

**Sputum culture conversion** – sputum culture obtained at the end of the intensive phase of therapy has no growth of *M. tuberculosis*. The end of the intensive phase of therapy will be defined by completion of the required number of directly-observed doses (as defined in Section 3.1), rather than by a specific number of weeks of therapy. In order to assure that each subject will be evaluable for the primary endpoint, two sputum cultures will be obtained at the end of the intensive phase of therapy. These two cultures must have been obtained (a) 0-7 days after the completion of the intensive phase of therapy (preferably, one on the day of completion and one within 7 days of completion), and (b) prior to receiving more than one dose of continuation phase therapy. Sputum culture conversion will be based on the results of both sputum cultures performed at the end of the intensive phase of therapy.  **Both sputum cultures, if evaluable, should be negative for *M. tuberculosis* in order to conclude that sputum culture conversion was achieved.** Sputum cultures that are overgrown by bacteria and/or yeast will be considered unevaluable. Subjects who are unable to produce a specimen for sputum culture despite an attempt with sputum induction will be considered to have had a negative culture on that date.

**Safety and tolerability endpoints** – the primary endpoint for the analysis of safety and tolerability will be the proportion of patients who discontinue the assigned study regimen for any reason. Other aspects of safety and tolerability that will be assessed as secondary endpoints include mortality, the occurrence of Grade 3 and 4 toxicities and the rate and types of toxicity thought related to study drug by the investigator.

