**Treatment failure** – a positive sputum culture after completion of 4 months of TB treatment. All treatment failure isolates will be compared to the initial isolate using DNA fingerprinting. A single positive culture having a different DNA fingerprint than the initial isolate will be considered a false-positive culture (due to cross-contamination) and will not be counted as a case of treatment failure.

- 1. Randomization

Eligible patients will be randomized in a 1:1 ratio to the arms. Randomization will be stratified by geographic continent and by the presence of cavitation on the chest radiograph used for screening purposes. Cavitation is defined as a gas-containing lucent space at least 1 cm in diameter within the lung parenchyma surrounded by an infiltrate or fibrotic wall greater than 1 mm thick seen on a standard chest radiograph (cavitation seen only on chest CT, if done, does not satisfy this definition).  Cavities must be distinguished from pulmonary cysts, which are usually thin walled, well-marginated lesions.

- 1. Sample Size Calculation

The culture conversion rate at 8 weeks among patients with initial sputum smear-positivity treated with HRZE who enrolled into TBTC Study 22 was 73.6% (419/574). We hypothesize that the effects of using a fluoroquinolone in place of isoniazid will improve the potency of the intensive phase of therapy by approximately that of the addition of pyrazinamide (mean of 12.7%, see Table 7). To detect an increase in culture conversion from 75% to 88% with a two-sided test at the 0.05 level with 80% power requires 154 patients per group. We will increase this by 25% to compensate for missing cultures, drug resistance, etc. Therefore there will be 205 patients in each of the two arms, 410 patients in the entire study. If, near the culmination of the intended enrollment of 410 patients to achieve 308 evaluable patients, it is determined that patient dropout, missing cultures, etc has exceeded the 25% estimate, then a proportionate number of additional patients will be recruited to retain statistical power.

- 1. Patient Selection

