End of intensive phase study visit –As above, the end of the intensive phase of therapy is defined by number of doses (40 to 44 doses, as defined in Section 3.1). When a patient has completed the assigned intensive phase, the monitoring blood tests will be obtained (complete blood count and serum AST, total bilirubin, and creatinine). Visual acuity and color vision testing, per standard site practice, will be repeated. In addition, two sputum cultures will be obtained for assessment of the sputum culture conversion, the primary endpoint of the trial. These specimens must be obtained on the day of completing the intensive phase of therapy or up to one week after completion, but before more than one dose of continuation therapy has been given. The two sputum specimens can be obtained on the same day.

- - 1. Study visits – continuation phase of therapy

Month 3 – Patients will have an assessment for delayed toxicity from the intensive phase of therapy. This will consist of a symptom-driven examination, visual acuity and color vision testing per standard site practice, and laboratory testing (complete blood count and serum AST, total bilirubin, and serum creatinine). A sputum specimen will be obtained for culture.

Months 4 through 6 (4 through 9 for those with extended therapy) - Patients will have study visits monthly during the continuation phase of therapy. Sputum cultures will be obtained at each study visit during the continuation phase of therapy until there have been 2 consecutive negative cultures. Laboratory testing, other than sputum cultures, will be at the discretion of the principal investigator. The study will end upon completion of 18 weeks (or 30 weeks for individuals with cavitation on initial chest radiograph plus positive sputum culture at 2 months of treatment) of an ATS/IDSA/CDC continuation phase therapy regimen and a related study visit. At each study visit during the continuation phase of therapy, patients will be asked about what medications they have been taking and if they have had any illnesses since the last visit.

- - 1. Scheduled unblinding of study treatment regimens

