For other grade 4 toxicities, the study drugs will be temporarily held and may be restarted or permanently stopped at the discretion of the investigator. Toxicities graded 3 or 4 by the Common Toxicity Criteria and occurring during study therapy will be documented on the Adverse Event Form, according to the criteria described in the next three sections. The maximum level of toxicity reached will be clearly indicated.

- 1. Criteria for discontinuation of study drugs

Certain events or conditions may necessitate temporary or permanent discontinuation of the study medication. Patients who experience such events or conditions, however, will still be "on study" and will be followed until study completion. Any patient for whom the study medication is temporarily discontinued will be restarted on study medication as soon as possible. Study regimens will be discontinued and non-study regimens will be used with continued study followup for patients who fail to respond to study therapy either clinically and/or bacteriologically, for patients in whom treatment-emergent drug toxicity warrants discontinuation of study therapy, and for patients who become pregnant. If study drugs are permanently discontinued, further antituberculous therapy may be administered at the investigator's discretion. These patients will be followed in the study for a maximum of 6 months of TB treatment, according to the guidelines and time-points established in the protocol, starting from the date of initiation of Study 28 intensive phase treatment.

- 1. Criteria for temporary discontinuation of study therapy
- Development of a toxicity that, depending on its nature and severity, requires temporary discontinuation of the study medication until the toxicity resolves as indicated in the preceding toxicity management section.
- Development of another medical condition that makes the administration of the study drug inadvisable. The decision to temporarily discontinue the study medication in this situation will be at the investigator's discretion. The period during which the patient is off study medication will be as short as clinically possible.
  1. Criteria for permanent discontinuation of study therapy
- Development of a toxicity that warrants permanent discontinuation of any study drug (refer to section on “Management of Adverse Events”).
- The patient refuses further therapy.

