Patients with treatment failure (see section 3.5) will be managed with an individualized treatment regimen at the discretion of the investigator. For each patient with treatment failure, drug susceptibility testing at the CDC will be performed for one *M. tuberculosis* isolate from sputum obtained after completion of 4 months of therapy. This drug susceptibility test result will be compared with that of the patient’s initial isolate. Patients with treatment failure will be followed in the study for a maximum of 6 months of TB treatment, according to the guidelines and time-points established in the protocol, starting from the date of initiation of Study 28 intensive phase treatment.

1. **EVALUATION**
   1. Data analysis

Comparison of baseline characteristics of treatment and control groups using chi-square test for categorical variables and t-test for continuous variables will be undertaken to evaluate for potential patient differences. Analysis of primary and secondary endpoints will be analyzed primarily as proportions and compared using chi-square or Fisher’s exact test, as appropriate. Multivariate proportional hazards regression will be used to identify independent risk factors for sputum culture conversion, and to adjust for any differences in baseline characteristics.

Since a percentage of subjects may drop out or be lost to follow-up in our clinical trial, imbalances may result that "undo" the effects of randomization. If there were no dropouts or subjects lost to follow-up, the effects of randomization would tend to make the experimental and control arms comparable with respect to possibly important predictors of the endpoint of interest. However, if there are drop-outs or subjects lost to follow-up, the two treatment groups may not be directly comparable at the end of the follow-up period, particularly if dropping out or being lost to follow-up are associated with the study regimen assignment or other potentially important predictors of the endpoint. Therefore, we plan to look at these subjects for potential differences in comparison to those who remained in the study.

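### A non-responder switched under section 5.6 whose culture clears before month 4 counts as a non-failure under section 3.5

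*Protocol*

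**What the plan says.** Comparing failure between regimens is a stated secondary objective (Secondary Objectives): "To compare the rates of treatment failure of the moxifloxacin regimen and the isoniazid regimen". Section 3.5 (Study Endpoints) defines failure as "a positive sputum culture after completion of 4 months of TB treatment", and discounts a single positive culture whose DNA fingerprint differs from the initial isolate.

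Section 5.6 (Criteria for discontinuation of study drugs) says that "non-study regimens will be used with continued study followup for patients who fail to respond to study therapy either clinically and/or bacteriologically". It gives no criterion and no time point for non-response. For permanent discontinuation it adds: "These patients will be followed in the study for a maximum of 6 months of TB treatment". Section 5.12 covers patients who already meet the definition: "Patients with treatment failure (see section 3.5) will be managed with an individualized treatment regimen".

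The main safety and tolerability endpoint in section 3.5 is the "proportion of patients who discontinue the assigned study regimen for any reason". The synopsis lists the same endpoint among the primary endpoints and gives it a window: "The proportion of patients who discontinue assigned study therapy for any reason during the first 2 months".

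**The concern.** The failure comparison is meant to show whether one regimen leaves more patients uncured on treatment. Section 5.6 allows the investigator to act on poor response before month 4, and section 3.5 does not treat that action as an outcome. If the replacement regimen works, the patient enters the comparison as a success of the randomised arm. The arm with more early non-responders then looks better on failure than it is.

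The same patient, if switched within 2 months, raises that arm's count of any-reason discontinuations. The endpoint as worded does not show whether the stop was for lack of response, toxicity or refusal. Section 5.12 does not recover the patient for the failure count, because it begins from the section 3.5 definition.

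**Working it through.** **Following one patient through the text.** Take a patient moved to a non-study regimen for non-response.

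1. The move itself is not a failure. Section 3.5 names one qualifying event, a positive culture after 4 months.
2. Follow-up continues for up to 6 months of TB treatment (section 5.6). The continuation-phase visit schedule says: "Sputum cultures will be obtained at each study visit during the continuation phase of therapy until there have been 2 consecutive negative cultures". A patient who stays positive is therefore still being sampled after month 4.
3. Section 3.5 refers to months of TB treatment, not months on the assigned regimen. If the culture is still positive after month 4, the patient is a failure. If it cleared before then and stays negative, the patient is a non-failure.
4. If the move came within the first 2 months, the patient is also a discontinuation event under both the synopsis and section 3.5. Neither makes an exception for non-response.

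**Expected number of culture-defined failures.** The plan gives no figure for this comparison. The planned total is 410, or 205 per arm, from 154 / (1 − 0.25) = 205.3. Table 10 reports 2 failures in 3177 patients with drug-susceptible disease and 1 in 172 with isoniazid resistance.

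- Drug-susceptible rate: 410 × 2/3177 = 0.26 failures in the whole trial. The chance of none at all is (1 − 2/3177)^410 = 0.77.
- Isoniazid-resistant rate, as a high reference only: 410 × 1/172 = 2.4. Patients with isoniazid-resistant isolates leave the study under section 5.2.

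**Possible number of switched patients.** The protocol gives no rate. As an assumption only, 1% to 5% of an arm would be 205 × 0.01 = 2.1 to 205 × 0.05 = 10.3 patients.

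To show how the count depends on what happens after the switch, assume 5% switched in the control arm and 2% in the moxifloxacin arm (10.3 and 4.1 patients):

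| Share still positive after month 4 | Failures counted, control | Failures counted, moxifloxacin |
| --- | --- | --- |
| 0 | 0 | 0 |
| 0.5 | 5.1 | 2.1 |
| 1 | 10.3 | 4.1 |

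The same non-responders give anything from no failures to all of them, depending only on how well the replacement regimen works. Against a background near 0.26, even two or three such patients matter.

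**The case against.** Sections 3.5 and 5.6 do not strictly contradict each other, since one defines an endpoint and the other governs management. A culture-only failure endpoint, checked by fingerprint and assessed whatever the regimen, is an objective and legitimate choice. Non-response under section 5.6 has no criterion, so counting it brings in judgement. With about 0.26 expected events, no definition will support a firm between-arm conclusion. A table of discontinuations by reason is routine content for a statistical analysis plan. All of this stands. It is why the culture-based definition should stay and why the point is a modest one. The failure definition itself, however, is fixed in the protocol, and as written it lets a successful switch hide lack of response.

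A reader might infer more than the text supports:

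- **That a switched non-responder can never be a failure.** Section 3.5 is not tied to the assigned regimen, and follow-up and cultures continue, so a patient positive after month 4 counts.
- **That lack of efficacy is scored only as intolerance.** The endpoint is openly an any-reason one. Mortality, Grade 3 and 4 toxicity and drug-related toxicity are separate endpoints in section 3.5, and a stop for non-response alone does not enter the toxicity ones.
- **That everyone culture-positive at 8 weeks is a candidate for a switch.** The planning rates give 205 × 0.25 = 51 and 205 × 0.12 = 25 such patients. The protocol does not treat that result as non-response needing a non-study regimen: with cavitation it lengthens continuation therapy, and without cavitation it specifies no change. The specimens are also taken at or after the end of the intensive phase, so their results cannot prompt a switch within it.

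**Conclusion.** The point holds in limited form. A patient switched for non-response whose culture clears before month 4 is a non-failure in a comparison that is a stated secondary objective. A switch within 2 months is also an any-reason discontinuation, not distinguished from toxicity or refusal.

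The size of the effect cannot be computed from the protocol and is probably small. The 1% to 5% switch rate is an assumption without a source, and using Table 10 assumes that its failure rate carries over to this trial. The case for acting is that the expected failure count is so low that a few reclassified patients could change the comparison, and that the remedy is cheap. The culture-conversion endpoint and the sample size are not at issue here.

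**What to change.** - Keep the culture-based definition in section 3.5 and report it as now.
- Beside it, pre-specify a composite failure outcome: culture-defined failure, or a change to a non-study regimen under section 5.6 that is recorded as being for clinical or bacteriological non-response. Date the event at the change and count it regardless of later cultures. Show the two components separately.
- Require the reason to be recorded while the investigator is still blinded, before any request under section 5.9.
- Record the reason for every discontinuation, and report the any-reason endpoint split into non-response, toxicity or intolerance, refusal, and other. Section 5.4 already puts study drug discontinuation on the Adverse Event Form but does not say that the reason is coded.
- Reconcile sections 3.5 and 5.6 so that they say how such a change of regimen is classified.

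The cost is a few sentences in sections 3.5 and 6.1 and one coded field. The downside is that the added component rests on blinded investigator judgement, which is why it is shown separately and does not replace the culture-based result. No treatment rule changes.
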